### Measurement of clinical outcomes

Baseline demographic characteristics, including gender, age, education level, occupation, smoking history, allergy history, family medical history, history of diabetes, and current use of analgesics, will be assessed, in addition to patient measurements such as height, weight, the level of lumbar disc herniation, and the severity of nerve compression measured by Pfirmann grading system base on lumbar MRI (Grade I: Herniated disc in contact with the nerve root without displacement; Grade II: Herniated disc in contact with the nerve root, no nerve root displacement; Grade III: Herniated disc in contact with the nerve root, causing posterior displacement of the nerve root; Grade IV: Herniated disc in contact with the nerve root, compressing it against the posterior wall of the spinal canal) (Majeed et al., 2016). Laboratory parameters, including fasting blood glucose and morning serum cortisol levels will also be measured. Pain intensity will be evaluated using the NRS for both low back pain and leg pain. The Oswestry Disability Index (ODI) and Roland-Morris Disability Questionnaire (RMDQ) will be used to assess functional disability. Generalized Anxiety Disorder 7 (GAD-7) and Patient Health Questionnaire 9 (PHQ-9) were used to assess anxiety and depression.

Follow-up assessments will be conducted at post-injection day 1, week 1, week 2, week 4, week 8, and week 12 (Table 1).

**TABLE 1 T1:** Schedule of enrolment, interventions, and assessments.

Timepoint	Enrolment	Baseline	Allocation	Follow up					
	​	​	0	*Day1*	*Week* *1*	*Week* *2*	*Week* *4*	*Week* *8*	*Week* *12*
Enrolment									
Eligibility screen	X	​	​	​	​	​	​	​	​
Informed consent	X	​	​	​	​	​	​	​	​
Allocation	​	​	X	​	​	​	​	​	​
Interventions									
Dexamethasoe palmitate	​	​	X	​	​	​	​	​	​
Combined betamethasone	​	​	X	​	​	​	​	​	​
Assessmens									
*Pain intensity (NRS score)*	​	X	​	X	X	X	X	X	X
*ODI score*	​	X	​	​	​	​	X	X	X
*RMDQ score*	​	X	​	​	​	​	X	X	X
*PHQ-9*	​	X	​	​	​	​	X	X	X
*GAD-7*	​	X	​	​	​	​	X	X	X
*Serum cortisol* *Levels blood glucose*	​	X	​	​	​	​	X	​	​
*Satisfaction*	​	​	​	​	​	​	X	​	​
*Adverse event*	​	​	​	X	X	X	X	X	X

The primary outcome of this study is leg pain measured by NRS score which is measured on a scale of 0–10, with 0 indicating “no pain” and 10 indicating “the worst pain imaginable” at 4 weeks after procedure.

The secondary outcomes are:

Pain: NRS scores at 1 week, 2 weeks, 8 weeks, and 12 weeks post-injection.

Functional disability: ODI and RMDQ at 4 weeks, 8 weeks, and 12 weeks post-injection.

Mental health assessment: GAD-7 and PHQ-9 at 4 weeks, 8 weeks, and 12 weeks post-injection.

Biochemical markers: Morning serum cortisol levels at 4 weeks post-injection. For participants with a pre-existing diagnosis of diabetes, fasting blood glucose will be monitored daily for seven consecutive days post-injection.

Patient satisfaction: Patient satisfaction will be evaluated at 4 weeks post-injection using a structured questionnaire. Satisfaction will be rated on a five-point Likert scale: very dissatisfied, dissatisfied, neutral, satisfied, and very satisfied. In addition, patients will provide a global impression of treatment effect, categorized as: marked improvement, moderate improvement, slight improvement, no change, mild deterioration, moderate deterioration, or severe deterioration.

Throughout the follow-up period, patients will be allowed to continue their pre-existing medication regimens. Concomitant medication use, including nonsteroidal anti-inflammatory drugs (NSAIDs), tricyclic antidepressants (TCAs), and gabapentinoids, will be recorded in detail at each visit, including type, dose, frequency, and duration.

Incidence of adverse events defined as any unintended and harmful outcome that occurs during or after the procedure, which may be directly or indirectly associated with the intervention.

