## Methods and analysis

### Study design

This is a two-arm multi-center, non-inferiority, randomized double-blind controlled trial. Patients with clinically confirmed lumbar disk herniation and radicular pain will be randomly assigned to one of two treatment arms: image guided epidural injection of DEP or combined betamethasone through an interlaminar or transforaminal approach. Follow up will be conducted at 1 day, 1 week, 2 weeks, 4 weeks, 8 weeks, and 12 weeks post-treatment. Pain intensity will be evaluated at all follow up time points, functional outcomes and mental health will be evaluated at 4 weeks, 8 weeks, and 12 weeks follow-up time points. Safety outcomes, including side effects and adverse events will be assessed at 1 day and 4 weeks after treatment. For patients with a pre-existing diagnosis of diabetes, fasting blood glucose levels will be monitored daily for seven consecutive days postoperatively to evaluate the impact of steroids on glycemic control. A repeat injection will be administered based on the patient’s response at 4 weeks of follow-up.

Approval for this study was obtained from the Research Ethics Committee of all the center (approval reference number: 2024-457, 2025-251001, 2024K095, KY-2024-003-02, 2025-06, 2024-41, 2025-002). The trial was registered in the Chinese Clinical Trial Registry (Trial number: ChiCTR2400093970, https://www.chictr.org.cn, Chinese Clinical Trial Registry, 2024-12-15) and the trial protocol followed the ‘Standard Protocol Items: Recommendations (SPIRIT) guideline (Schulz et al., 2010). Patient consent was obtained after enrollment in accordance with the Declaration of Helsinki.

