### Repeat injection

At the 4-week follow-up, patients who experience ≥50% reduction in leg pain from baseline may be considered for a repeat injection. The medication and route of administration for the repeat injection will be the same as those used in the initial treatment. Patients may also choose to receive the alternate study medication for the repeat injection. Decisions regarding repeat injections will be made collaboratively between the physician and the patient and documented in the case report form. Each patient will receive one injection initially, with a maximum of two injections allowed during the study period.

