### Adverse events

The occurrence of adverse events (AEs) will be reported by treatment group. A Chi-square test or Fisher’s exact test (for categorical data) will be used to compare the occurrence of AEs between the two groups.

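### The assessment schedule follows the first injection only, so adverse events are collected less systematically after a second injection, yet the adverse-event comparison does not separate the two periods

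*Protocol article*

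**What the plan says.** **Schedule.** Under Measurement of clinical outcomes: "Follow-up assessments will be conducted at post-injection day 1, week 1, week 2, week 4, week 8, and week 12 (Table 1"). Table 1 has a single time axis starting at allocation (0). Both drugs are marked only at 0, and no row or column covers a second injection. Adverse events are marked at all six follow-up visits. The cortisol and glucose row is marked at baseline and week 4 only.

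**Second injection.** The Repeat injection section states: "At the 4-week follow-up, patients who experience ≥50% reduction in leg pain from baseline may be considered for a repeat injection". Each patient has one injection initially, "with a maximum of two injections allowed during the study period". The section says that the repeat uses the same medication and also that patients may choose the alternate study medication.

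**Safety timing elsewhere.** Study design gives a shorter list than Table 1: "Safety outcomes, including side effects and adverse events will be assessed at 1 day and 4 weeks after treatment". Among the secondary outcomes: "Biochemical markers: Morning serum cortisol levels at 4 weeks post-injection". For patients with known diabetes, "fasting blood glucose will be monitored daily for seven consecutive days post-injection". None of these says whether the clock restarts after a second injection.

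**Collection outside the table.** Data and safety monitoring adds questioning about specific symptoms immediately after the injection and by telephone during follow-up, and recording of spontaneous reports at any time. The calls have no dates.

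**Analysis.** Under Adverse events: "The occurrence of adverse events (AEs) will be reported by treatment group", with a chi-square or Fisher's exact test between the groups. Events after first and second injections are not distinguished.

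**The concern.** Safety is part of the reason for the trial: the Introduction and Discussion present a possible safety advantage of dexamethasone palmitate, and the Discussion names adverse events and cortisol as safety endpoints. An adverse-event comparison is easiest to interpret when every exposure is observed with the same intensity. As printed, the first injection is observed closely in its early period and the second is not. The Discussion mentions transient neurological symptoms as a hazard of the procedure. Such an event could resolve before a visit four weeks later.

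Two features make the period after week 4 harder to read by randomised group. A second injection depends on the week-4 response, which is itself a post-randomisation outcome. It may also be the other study drug, so an event counted under one arm may follow the other arm's steroid. Cortisol is sampled at the visit at which a repeat is first considered, so the result describes one injection, although the trial permits two.

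**Working it through.** **Inputs.** Adverse-event marks in Table 1: days 1, 7, 14, 28, 56 and 84. Cortisol marks: baseline and day 28. Maximum of two injections (Repeat injection). Assumption: the second injection is given at about day 28, since eligibility is judged at the 4-week visit.

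**Step 1. Scheduled assessments after each injection (time from second injection = study day − 28).**

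| | After first injection | After second injection (day 28) |
|---|---|---|
| Adverse-event visits in the next 28 days | days 1, 7, 14, 28: four | day 56, i.e. 56 − 28 = 28 days later: one |
| Early visits (day 1, week 1, week 2) | 3 of 3 | 0 of 3 |
| Later adverse-event visits | days 56 and 84 | day 84, i.e. 84 − 28 = 56 days later |
| Cortisol samples | one (day 28) | none |

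**Step 2. The shorter list in Study design.** With day 1 and week 4 counted from the first injection only, no scheduled safety assessment follows a second injection. If that clock restarts, there are two (study days 29 and 56). The answer depends on which section is followed and how it is read.

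**Step 3. Does a restarting clock rescue Table 1?** Early visits after a second injection would fall on study days 28 + 1 = 29, 28 + 7 = 35 and 28 + 14 = 42. Full follow-up would run to week 4 + 12 = 16, with a cortisol sample at week 8. Table 1 has none of these, and the Abstract and Study design end follow-up at 12 weeks. The printed table therefore favours the first-injection clock, though the text does not say so.

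**Step 4. How many patients?** The article gives no expected repeat rate. The denominator is its own sample size, which reproduces: 2 × (1.960 + 1.282)² × 2.2² / 1² ≈ 101.7, so 102 per group; 102 / 0.90 = 113.3, so 114 per group and 228 in total. This point does not affect that figure.

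For scale only, the share eligible is P(week-4 NRS ≤ half of baseline). With the planned SD of 2.2, a fixed baseline b and a week-4 mean m, this is Φ((0.5b − m)/2.2). Both b and m are assumed:

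- b = 5, m = 5: Φ(−2.5/2.2) = 0.128, about 29 of 228
- b = 6, m = 3: Φ(0) = 0.50, 114 of 228
- b = 7, m = 2: Φ(1.5/2.2) = 0.752, about 172 of 228

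Eligibility thus runs from about 13% to 75% over b = 5 to 7 and m = 2 to 5. It is only a ceiling on uptake, because the repeat is optional: "patients who experience ≥50% reduction in leg pain from baseline may be considered for a repeat injection". The counts in Step 1 need none of these assumptions about b and m.

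**The case against.** The strongest reply is that Data and safety monitoring already covers second injections. Symptoms are asked about immediately after the injection and by telephone, and spontaneous reports are taken at any time. That stands. A reader might infer from Table 1 that second injections have no safety assessment, or that their early harms are bound to be under-recorded. The document supports neither inference. What it supports is less structured collection, because no contact is fixed at day 1, week 1 or week 2 after a second injection.

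A reader might also infer that about half of the patients are affected. No figure in the document supports this. The range above is wide, rests on assumed means, and bounds eligibility rather than uptake.

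It can be said that both arms share the schedule, that participants and assessors are blinded, and that a comparison of occurrence is naturally a count of patients, so a missed event matters only if that patient has no other recorded event. This also stands. Incomplete capture becomes differential between arms only if repeat rates differ, and no such difference is shown. A biased comparison is therefore a possibility, not a finding.

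On cortisol, the outcome is already labelled as a 4-week result, and sampling before any repeat keeps the randomised comparison clean. That is a reason to keep the sample and describe it accurately; no passage claims that it covers two injections.

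Finally, call dates and the analysis window might be left to fuller documents. That explains an omission. It does not remove the difference between Study design and Table 1, or the absence of any second-injection entry in a schedule that is printed mark by mark.

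**Conclusion.** The point holds as a cheap improvement. On the printed schedule, a second injection at about week 4 has one scheduled adverse-event assessment in the following 28 days, against four after the first. It has none of the three early visits and no cortisol sample. Early events can still be captured through the other routes, but less systematically. After week 4, the by-group comparison mixes unequal ascertainment and, for patients who choose the alternate medication, possibly the other steroid. The number of patients involved cannot be derived from the document, and no bias between arms is demonstrated. The week-4 primary endpoint and the sample size are unaffected. The conclusion rests on reading Table 1 as counted from the first injection, which its single axis and 12-week end favour.

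**What to change.** 1. **Reconcile the text.** Bring Study design, Table 1, the secondary-outcome list, Repeat injection, and Data and safety monitoring into agreement on when adverse events are assessed, and on whether adverse-event, glucose and cortisol assessments restart after a second injection.
2. **Date the calls already planned.** In Data and safety monitoring, and as a row in Table 1, place telephone adverse-event contacts at day 1, week 1 and week 2 after any second injection.
3. **Separate the periods in the analysis.** Under Adverse events, make first injection to week 4 the main between-group comparison, with the week-4 assessment made before any second injection. Keep the 12-week summary by group. Report events after a second injection separately, by drug received, with the number of second injections as denominator.
4. **Describe cortisol accurately.** Call the week-4 value a single-injection result.

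The cost is up to three extra calls per re-injected patient, one table row and a few sentences. The downside is some additional site work and a shorter window for the main adverse-event comparison; retaining the 12-week summary limits what is lost. These changes concern data collection and reporting. Whether any further clinical monitoring is needed is for the investigators to decide.

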### Exclusion criteria

Individuals with known allergies to the study medication.A history of psychiatric disorders.Inability to comprehend the study details, participate in scale assessments, or comply with follow-up visits.Presence of comorbid conditions that could affect the assessment of treatment efficacy, specifically conditions that could cause leg pain (e.g., Parkinson’s disease, diabetic peripheral neuropathy, lower limb thrombosis).Severe cardiovascular diseases that impair daily activities or affect functional assessment scores.Unstable spondylolisthesis (vertebral displacement >3 mm or endplate angle change >15° on dynamic lumbar spine radiographs), or Grade 3 and above spondylolisthesis with instability.Severe osteoporosis with vertebral compression fractures in the segment intended for injection.Malignant tumors with spinal metastasis.Pregnant or breastfeeding women, women planning pregnancy soon, or women whose partners are planning pregnancy.Other contraindications to injection treatments, such as current infection at the puncture site, severe coagulopathy and resulting complications (e.g., gingival bleeding)Recent (within 3 months) history of spinal intrathecal injections.Upcoming surgical plans within the next 3 months.Platelet count below 50 × 10^9^/L or concurrent use of anticoagulant or antiplatelet medications.Presence of the following conditions: posterior subcapsular cataract, glaucoma, herpes simplex keratitis, poorly controlled diabetes (fasting blood glucose ≥7 mmol/L), acute myocardial infarction, peptic ulcer, tuberculosis, infections without effective antibiotic treatment, systemic fungal infections, electrolyte imbalances, recent abdominal surgeries, or thrombosis.

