### Strategies to improve adherence to interventions

The use of non-steroidal anti-inflammatory drugs (NSAIDs) or tramadol as rescue medication is permitted during the study period. Allowed medications are limited to ibuprofen (maximum 1,200 mg/day) or naproxen (maximum 1,000 mg/day) or tramadol at a maximum 400 mg/day administered orally in divided doses as needed for pain control. Patients are instructed to use rescue medication at the lowest effective dose and to maintain consistent usage patterns, when possible, throughout the follow-up period.

The type, dose, and frequency of NSAID use will be recorded at each follow-up visit and included in the statistical analysis to assess potential confounding effects.

Additional invasive interventions targeting lumbar disc herniation, such as nerve blocks or spinal cord stimulation, are not permitted during the study period, as they may directly influence pain and functional outcomes.

All clinical staff involved in administering the intervention will receive comprehensive training on the protocol. Each center is also provided with easy access to detailed protocol documentation, including visual aids and quick-reference guides that summarize key points of the protocol. Periodic audits will be conducted at each center to review adherence to the protocol.

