### Secondary outcome analysis

The secondary outcomes of this study are leg pain scores at multiple follow-up time points, functional disability (ODI and RMDQ), mental health assessment (GAD-7 and PHQ-9), and biochemical markers. For leg pain, the NRS scores for leg pain will be analyzed at each follow-up time point using Mixed-Effects Linear Models to account for repeated measurements and intra-patient correlation. This model includes fixed effects for treatment, time, and the interaction between treatment and time. Random intercepts are used to model individual variability over time. Functional disability scores are assessed via changes in ODI and RMDQ measured at 4, 8, and 12 weeks using Mixed-Effects Linear Models. Both measures are treated as continuous variables, and the analysis accounted for repeated measurements within patients. Mental health assessments will be completed using GAD-7 and PHQ-9 anxiety and depression scores, respectively, using Mixed-Effects Linear Models at 4, 8, and 12 weeks. Serum cortisol levels at 4 weeks will be compared between treatment groups using Student’s t-test for normally distributed data, and the Mann–Whitney U test for non-normally distributed data after assessment of normality.

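### Users of non-spinal corticosteroids can be enrolled and remain exposed when week-4 cortisol is drawn, and the planned cortisol test takes no account of it

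*Protocol article*

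**What the plan says.** **Eligibility.** The Exclusion criteria section is a detailed list. Its nearest item to prior steroid exposure is "Recent (within 3 months) history of spinal intrathecal injections", which covers one route only. The only drug classes whose use excludes a patient are those in "concurrent use of anticoagulant or antiplatelet medications". The item on comorbidities that could disturb the efficacy assessment is narrowed to "specifically conditions that could cause leg pain". Nothing addresses oral, parenteral, intra-articular or other non-spinal corticosteroids, or adrenal disease.

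**During follow-up.** Measurement of clinical outcomes states: "Throughout the follow-up period, patients will be allowed to continue their pre-existing medication regimens". No class is excepted. The same section adds: "Concomitant medication use, including nonsteroidal anti-inflammatory drugs (NSAIDs), tricyclic antidepressants (TCAs), and gabapentinoids, will be recorded in detail at each visit". The list is open, but corticosteroids are not named in it. Strategies to improve adherence to interventions does set a limit ("Allowed medications are limited to ibuprofen (maximum 1,200 mg/day) or naproxen (maximum 1,000 mg/day) or tramadol"), but that limit is on rescue medication, not on what patients already take.

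**Analysis.** Morning cortisol at week 4 is a secondary outcome, and the Discussion counts it among the safety outcomes. Secondary outcome analysis says: "Serum cortisol levels at 4 weeks will be compared between treatment groups", by t-test or Mann–Whitney test. Table 1 shows that cortisol is also measured at baseline, but the stated test does not use it. The primary model has terms for treatment, time, their interaction, centre and baseline NRS. The only medication said to enter an analysis is NSAID use: "The type, dose, and frequency of NSAID use will be recorded at each follow-up visit and included in the statistical analysis".

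**The concern.** Both arms receive a corticosteroid, and cortisol is the one laboratory marker compared between them at week 4. A corticosteroid taken for another reason acts on the same marker. Read together, the criteria and the medication rule let a site enrol a patient on a daily oral steroid, inject the study drug, and draw cortisol at week 4 while the tablets continue. That value may say little about the injected formulation. Part of the case for dexamethasone palmitate is a possible safety advantage, so a noisy or attenuated cortisol comparison weakens evidence that the trial sets out to provide.

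There is a second, smaller consequence for leg pain. If a background corticosteroid partly controls pain in both arms, the difference between the study drugs shrinks in those patients. In a non-inferiority trial, shrinkage makes the claim easier to reach.

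**Working it through.** **Inputs from the article** (Study sample size): SD 2.2, margin 1, true difference 0, one-sided alpha 0.025, power 0.90, 10% loss.

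**Assumptions, not in the article:** the share of steroid users *p*; the cortisol SD and the shift in users; the drug difference among users.

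**1. The plan's own figure.** n per group = 2 × 2.2² × (1.960 + 1.282)² / 1² = 101.7, so 102. Allowing for loss, 102 / 0.90 = 113.3, so 114. Both stated figures reproduce.

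**2. Cortisol: spread.** Assume SD 120 nmol/L and users 250 nmol/L lower, with the same spread in users. The SD ratio is √(120² + p(1−p) × 250²) / 120.

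- p = 3%: √(14,400 + 1,819) / 120 = 1.06
- p = 5%: √(14,400 + 2,969) / 120 = 1.10
- p = 10%: √(14,400 + 5,625) / 120 = 1.18

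The same quantity can be read as chance imbalance. With 102 per arm, the between-arm difference in the share of users has SD √(2p(1−p)/102), which is 3.1 percentage points at p = 5% and 4.2 at p = 10%. Multiplied by 250 nmol/L, that is a random shift with SD of about 7.6 and 10.5 nmol/L. This is the source of the inflation above, not an addition to it.

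**3. Cortisol: power over a range of shifts.** Work in SD units. Take a difference among non-users of 0.4544 SD, which gives 90% power at 102 per group. Users sit k SD lower, with half the spread and no treatment difference. The variance is (1−p) + 0.25p + p(1−p)k², and the standardised difference is (1−p) × 0.4544 / √variance.

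| Users | Standardised difference, k = 2 to k = 3 | Power, k = 2 to k = 3 |
|---|---|---|
| 2% | 0.43 to 0.41 | 87% to 84% |
| 5% | 0.40 to 0.37 | 82% to 74% |
| 10% | 0.36 to 0.31 | 73% to 60% |

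**4. Leg pain.** SE = 2.2 × √(2/102) = 0.308. Let the true deficit be 1 point in non-users and zero in users, which is the extreme case. The mean deficit among all enrolled is then 1 − p, and the chance of concluding non-inferiority is Φ(p/0.308 − 1.96). The second column lets users keep half the deficit, so p/2 replaces p.

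| Users | No deficit in users | Half the deficit in users |
|---|---|---|
| 0% | 2.5% | 2.5% |
| 2% | 2.9% | 2.7% |
| 5% | 3.6% | 3.0% |
| 10% | 5.1% | 3.6% |

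**The case against.** A reader might infer that the cortisol outcome as a whole is corrupted, or that the trial is tilted towards a false claim of non-inferiority. The documents support neither.

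- **No directional bias in cortisol.** Randomisation balances background steroid use in expectation. What remains is noise, attenuation and chance imbalance.
- **The leg-pain percentages are not a type I error for the trial's own estimand.** If 5% of patients have no drug difference, the true mean difference among those enrolled is 0.95, which is inside the margin. A conclusion of non-inferiority would be wrong only for the non-users.
- **Zero drug difference in users is extreme.** Entry requires an NRS score of at least 4, so an enrolled user has pain that the background steroid has not controlled. With half the deficit retained, the effect is small.
- **The share of users is unknown, and some criteria lower it.** Glaucoma, posterior subcapsular cataract, peptic ulcer and fasting glucose of 7 mmol/L or more all exclude, and each may remove some long-term users. That narrows the gap without closing it.
- **The SD inflation describes the t-test.** A distinct low-cortisol cluster could lead to the Mann–Whitney test instead, to which that figure does not apply.
- **Users may be identifiable.** Medication recording is open-ended, baseline cortisol is measured, and a separate analysis plan could say how to use both.

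These arguments limit the size of the point and make leg pain secondary. They do not remove it. The article sets out its exclusion list, gives an unqualified permission to continue medication, and names an unadjusted cortisol test. The issue is how those three stated rules combine, not detail left to another document.

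**Conclusion.** The point holds, mainly for week-4 cortisol. As written, the plan admits users of systemic or other non-spinal corticosteroids, lets them continue, and compares cortisol without regard to baseline level or steroid use. For the assumed SD and shift, the cost is an SD inflation of about 6% at 3% users and 18% at 10%. Over shifts of 2 to 3 SD, power falls from 90% to 82–74% at 5% users. With very few users the loss is minor.

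For leg pain, the most that can be said is that dilution runs in the direction that favours non-inferiority. It is small below about 5% users, even in the extreme case.

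All of these magnitudes are conditional on a share of users that the article does not give. The gap in the rules does not depend on it. The point is worth correcting, but it does not threaten the trial's primary conclusion.

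**What to change.** - **Eligibility.** Add a criterion stating how current and recent systemic or other non-spinal corticosteroid use at entry is handled, and reconcile it with the permission to continue existing medication and with the cortisol outcome. The clinical rule and the time window are for the sponsor to set. The change concerns who is enrolled and analysed; no patient need be told to stop a treatment.
- **Patients already enrolled.** Identify corticosteroid users from medication recorded before injection, so that the definition rests on baseline status and cannot be affected by the allocated drug. Leave them out of the cortisol comparison and the per-protocol set, and keep them in the ITT analysis. The baseline list in the article names current analgesics only, so check that the pre-injection record captures corticosteroids.
- **Cortisol analysis.** Adjust week-4 cortisol for baseline cortisol, which is already collected.

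The cost is a line or two of text and one covariate. The downside is the loss of a few otherwise eligible patients and a slightly narrower population.
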